### Plans to give access to the full protocol, participant-level data and statistical code {31c}

Participant data will not be made publicly available as the re-identifiable format allows participants to easily be identified.

### Oversight and monitoring

#### Composition of the coordinating centre and trial steering committee {5d}

The trial will be coordinated primarily by a research student investigator, who will be supervised by a post-doctoral researcher. Both are Accredited Exercise Physiologists based at UNSW. They will meet weekly prior to and during the trial to plan and discuss the progress of the trial.

#### Composition of the data monitoring committee, its role and reporting structure {21a}

The data monitoring committee will consist of three researchers who will be able to advise the researchers handling data on their responsibilities and procedures concerning data analysis and storage. Researchers on the data monitoring committee and researchers handling data will be independent from the trial sponsor and will have no competing interests.

#### Adverse event reporting and harms {22}

Participants will be strongly encouraged to inform the research team of any physical or mental harms caused by the programme, and the research team will report the adverse events to the UNSW Human Ethics Office within 72 h of becoming aware of the event.

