The *StandingTall* eHealth programme provides home-based exercise to improve balance and reduce fall risk [16]. Individuals will be provided with access to the programme and a manual on setting up and using the application. They will join a small group video call to receive assistance from a facilitator to set up the app and will be encouraged to contact the primary study investigator for assistance with any technological difficulties or queries. The app will provide participants with an individualised exercise programme that will suit their abilities, but remains challenging, based on a baseline balance assessment. This assessment will be completed in week 1 when the participants are guided to set up their *StandingTall* account. The programme will be progressed automatically based on the reported rate of perceived exertion through training. Exercises will train static and dynamic balance, stepping in different directions, functional strength and dual-task activities. Frequency, duration, intensity and dose of *StandingTall* training will be individualised to participants, but participants will be guided by facilitators to set goals around completing their exercise programmes with the aim of encouraging all to gradually complete a recommended dose of 2 h of balance training per week. Website analytics will track adherence data and time spent on the app data through individual logins.

Participants will also receive individualised support from allied health facilitators, including tailored aerobic and strength exercise programmes prescribed by Accredited Exercise Physiologists depending on participants’ health needs and activity interests. Exercise programmes will be designed to encourage participants to reach the physical activity guidelines of 150 min of moderate to vigorous activity, unless the participant indicates during goal setting that this volume is unrealistic for their abilities and/or circumstance [9].

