At the conclusion of the 10-week programme, the Facebook groups and *StandingTall* programme will remain accessible without input from facilitators. The waitlist control group will also have access after their final assessment at 14 weeks from baseline. They will join a private Facebook group (separate from the intervention group) and complete the facilitated intervention without answering additional questionnaires. Based on feedback from the intervention group, the researchers will be using the waitlist control programme to trial new features of the programme such as additional topics suggested.

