### Outcomes {12}

The primary outcome is psychological distress, and secondary outcomes include physical activity levels, social capital, cognition, concern about falling, loneliness, quality of life, physical functioning and exercise enjoyment. Participants will complete all questionnaires at baseline, week 11 (post-intervention) and at the 1-month follow-up point (see Table 3) so that change from baseline to post-intervention and change from baseline to the follow-up point can be evaluated. It will take approximately 45 min for participants to complete questionnaires at each time point. A demographics questionnaire will also be completed by participants at baseline only. This will ask participants about their age, the highest level of education completed, marital status, living situation, employment status, known medical conditions, their mobility around the house and outdoors, fall history, self-reported concern about falling and Facebook usage.

**Table 3 Tab3:** Timeline for data collection

	Pre-programme		Programme	Post-programme	
	Enrolment (< − 1 week)	Baseline (− 1 week)	Weeks 1–10	End of week 10	Follow-up (+ 4 weeks)

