#### Frequency and plans for auditing trial conduct {23}

Auditing of the trial will be conducted annually. The research team will fill in an annual monitoring form indicating trial status, adverse events, complaints and protocol deviations. This will be submitted to UNSW HREC.

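### Harms and falls are not ascertained systematically or comparably by arm: the stated rule asks for volunteered harms attributed to the programme, and nothing after baseline asks either arm about events

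*Protocol article*

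**What the plan says.** All references are to the protocol article.

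- **Adverse event reporting and harms {22}.** Collection: "Participants will be strongly encouraged to inform the research team of any physical or mental harms caused by the programme". Onward reporting: "the research team will report the adverse events to the UNSW Human Ethics Office within 72 h of becoming aware of the event". Recording by arm is not mentioned.
- **Frequency and plans for auditing trial conduct {23}.** "The research team will fill in an annual monitoring form indicating trial status, adverse events, complaints and protocol deviations". This form passes on events the team already knows about; it does not ask participants anything.
- **Intervention description {11a}.** StandingTall "provides home-based exercise to improve balance and reduce fall risk". On the control arm: "The waitlist control group will also have access after their final assessment at 14 weeks from baseline". Those participants then "complete the facilitated intervention without answering additional questionnaires".
- **Outcomes {12} and Table 3.** Falls appear once, within a demographics questionnaire given at baseline only, which covers "their mobility around the house and outdoors, fall history, self-reported concern about falling and Facebook usage". The only fall-related measure at later visits is the Icon-FES, which scores concern about falling and does not count falls.
- **Methods for additional analyses {20b}.** The baseline fall history defines a subgroup. No other use of it is stated.

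**The concern.** The request for harms has two filters. The participant must come forward unprompted, and must believe that the programme was the cause. A waitlist participant cannot pass the second filter before the final assessment, because there has been no programme to blame. The two arms are therefore observed under different rules.

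This matters because the intervention is home balance training, designed to stay challenging, in people aged 60 and over, and fall risk is part of the trial's rationale. A count gathered this way has no comparator and no denominator of people who were asked. It could support neither a statement that the programme is safe nor a statement that falls were more or less frequent with it.

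**Working it through.** The documents state no harm or fall rate, so there is no figure of the plan to reproduce. The check is mainly of text, followed by an illustration of size.

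**1. Is there another route that solicits events?**

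| Place | What it provides | Solicits events in both arms? |
|---|---|---|
| Harms {22} | Volunteered harms attributed to the programme | No |
| Auditing {23} | Annual form on known events | No |
| Outcomes {12}, Table 3 | Fall history at baseline only; Icon-FES later | No |
| Intervention {11a} | Group calls, weekday monitoring of the Facebook group | No; reaches the intervention arm during the comparison |
| Adherence {11c} | Private contact after two weeks of missed calls or exercise dose | No; reaches the intervention arm during the comparison |
| Discontinuing {11b} | Health changes that preclude exercise lead to exclusion from analysis | No; no method of finding them is stated |
| Table 3, K10 and EQ-5D | Distress and general health at both later visits | Both arms, but these are scores and not events |

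The informal routes may bring some events to light, but mostly in one arm, so they add to the asymmetry.

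**2. Effect of the attribution filter.** Assume 40 per arm (Sample size {14}), the same true event risk p in both arms, and a share a of intervention-arm events that is attributed to the programme and volunteered. Under the request as worded, and leaving aside events noticed by staff:

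- recorded, intervention = 40 × p × a; recorded, control = 0
- share of all events unrecorded = 1 − (40pa)/(80p) = 1 − a/2

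With p = 0.10 there are 4 true events in each arm:

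| a | Recorded, intervention vs control | Share unrecorded |
|---|---|---|
| 0.25 | 1 vs 0 | 87.5% |
| 0.50 | 2 vs 0 | 75% |
| 0.75 | 3 vs 0 | 62.5% |

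The share unrecorded does not depend on p. Equal true risks would show as events in one arm only.

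**3. How many falls are at issue.** Assume a yearly risk P of at least one fall of 20% to 40% and a constant hazard (neither is in the documents). Over 14 weeks the risk is 1 − exp(ln(1 − P) × 14/52):

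| P | 14-week risk | Expected fallers per 40 |
|---|---|---|
| 0.20 | 5.8% | 2.3 |
| 0.30 | 9.2% | 3.7 |
| 0.40 | 12.8% | 5.1 |

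**4. What asking everyone would give.** If all n people in an arm are asked and none reports an event, the one-sided 95% upper limit is 1 − 0.05^(1/n): 7.2% for n = 40, and 8.4% for n = 34 (half of the 68 required before dropout inflation). With volunteered reports the number asked is unknown, so no such limit can be given.

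**5. What it would not give.** Power to detect a doubling of the risks in step 3 (two-sided Fisher exact test, 5%) is 6%, 14% and 23% with 40 per arm, and 4%, 11% and 18% with 34 per arm.

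**The case against.** **This is a condensed article.** Event forms, definitions and tables by arm may sit in the full protocol or analysis plan. That is a fair defence of silence on those details, and none of them is counted here. It does not cover the rule that the article does state, which limits the request to harms attributed to the programme. Nor can an analysis plan recover events that nobody was asked about.

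**A reader might infer that an event is recorded only if volunteered and blamed on the programme, and that falls go wholly uncounted.** The documents do not support that. A fall that a participant blames on the programme and reports would be recorded. Staff may learn of others through calls, adherence contact or health changes. The annual form refers to adverse events without an attribution condition, and the 72-hour clock runs from awareness. What stands is that ascertainment is neither systematic nor alike in the two arms.

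**A reader might also infer that asking about falls would reveal a rise caused by the exercise.** Step 5 shows that it would not: even a doubling would usually be missed. The gain is honest description with a denominator.

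**Safety and fall rate are not stated outcomes.** This is correct, and leaving falls out of the efficacy outcomes of a trial about distress is a legitimate choice of scope. It limits the point to harms reporting and to any safety or falls statement drawn from it.

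**Data collection is over.** Trial status gives completion on 3 October 2022. New items therefore cannot be added for this trial, but the limit on what may be claimed remains.

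**Conclusion.** The point holds as a defect in how harms are ascertained. Followed as written, the plan produces a one-sided and unsystematic count of harms, and no count of falls that can be compared between arms. This follows from the wording of the harms section, the absence of any event item after baseline in Table 3, and the waitlist arm's lack of exposure until its final assessment. It needs no assumed rate.

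The size does rest on assumptions: about 2 to 5 fallers per arm of 40 over 14 weeks if 20% to 40% fall yearly at constant hazard. Numbers of that order justify reporting by arm, and do not support a test. The plan should be changed on this point, but the primary comparison on psychological distress is not affected by it.

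**What to change.** **For any further delivery or trial of the programme.** At post-intervention and follow-up, in both arms, ask the same three fixed items about the time since the last questionnaire: number of falls, number of falls with injury, and any health event needing medical care. Ask them regardless of perceived cause and judge relatedness to the programme separately. Tabulate by randomised arm with the number of people asked, labelled as description and not as a powered comparison. Keep volunteered reports as a supplement, listed apart.

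**For this trial, with data collection complete.**
- Tabulate by arm, at each visit, the number with K10 above 30 and the number with a K10 score. K10 is scheduled in both arms, so no new data are needed. Count every randomised participant with a score, including anyone whom section {11b} would exclude from analysis because health came to preclude exercise. The value 30 is the protocol's eligibility threshold and not a harm definition, and the table should say so.
- State in the report that harms were volunteered and attribution-based, with no event items after baseline.
- Make no comparative statement on safety or falls.

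**Cost.** Three items added to a questionnaire of about 45 minutes, and one table. Self-reported falls carry recall error. Participants are not blinded, and one arm has a fall prevention programme and regular staff contact, so recall and reporting may differ between arms. The report should name this as a limitation.

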#### Frequency and plans for auditing trial conduct {23}

Auditing of the trial will be conducted annually. The research team will fill in an annual monitoring form indicating trial status, adverse events, complaints and protocol deviations. This will be submitted to UNSW HREC.

#### Plans for communicating important protocol amendments to relevant parties (e.g. trial participants, ethical committees) {25}

Protocol modifications will first be submitted to the UNSW Ethics Committee for approval before implementation. If approved, trial participants will be informed of changes through an email from the investigators.

#### Dissemination plans {31a}

The findings of this trial will be disseminated through peer-reviewed publication(s) and academic conference presentations. These strategies will target academics and mental health and exercise professionals. Further social media will be used to reach this audience as well as the general public.

## Discussion

The *MovingTogether* programme combines a mental health-informed online health promotion programme delivered via social media [19] with an eHealth exercise-based fall prevention [17] and general physical activity programme to improve mental health by increasing physical activity. Physical activity programmes have demonstrated improvements in many indicators of mental health such as quality of life, psychological distress, depression and anxiety [56]. Research has shown that to increase adherence to exercise among older adults, programmes should focus on group cohesion and social support and should provide individualised health benefits and tailored advice [57, 58]. Lifestyle changes, including a reduction in physical activity [12], due to social isolation (e.g. during the COVID-19 pandemic), have highlighted the need for scalable, effective and innovative methods of achieving improvements in both the mental and physical health of older adults. Using technology for service delivery is an emerging area of research for mental healthcare [59], and it has been established that eHealth can be effective at promoting physical health in older adults [60].

### Limitations

It is likely that most of our participant sample will be those who are considered technologically literate and willing to try something new. While it is important that participants can use Facebook and the *StandingTall* programme, it will be difficult to evaluate the uptake, adherence and effect that this programme could have on a wider population, including those who do not currently engage in social media use. We have partially addressed this by releasing recruitment materials through print media, alongside the online sources as the main method of recruitment. Additionally, the result of subgroup analyses including the effect of the programme on those with high psychological distress and those who have greater adherence to the programme will have limited power.

## Conclusion

This RCT will investigate the efficacy of *MovingTogether*, a combined Facebook-delivered healthy lifestyle education and support programme, an eHealth fall prevention programme and tailored exercise. The findings will be used to inform the delivery of a potentially scalable online programme for adults aged 60+ to improve mental and physical health.

## Trial status

Protocol version 1.0 (1 July 2021). Recruitment started on 7 February 2022 and was completed on 10 June 2022. Data collection was completed on 3 October 2022. The authors note that the protocol was submitted to *Trials* on 29 April 2022 prior to the enrolment of the last participant on 10 June 2022. However, the trial was registered on the Australian New Zealand Clinical Trials Registry (ANZCTR) (ACTRN12621001322820p) on 29 September 2021, before the start of recruitment.

## Abbreviations

AEP: Accredited Exercise Physiologist
AQoL-6D: Assessment of Quality of Life
EI: Emotional intelligence
EPs: Exercise physiologists
ESSA APSS: Exercise Sports Science Australia Adult Pre-exercise Screening System
K10: Kessler 10
PA: Physical activity
PTSD: Posttraumatic stress disorder
RCT: Randomised controlled trial
RPE: Rate of perceived exertion
SIDAS: Suicidal Ideation Attributes Scale
SIMPAQ: Simple Physical Activity Questionnaire
